## 2. Methods and Design

### 2.1. Study Design

The study is cohort-prospective, non-randomized and non-interventional (Figure 1). It will assess the association between the predominant composition of the human gut microbiome and the response to immunotherapy treatment with PD-1 and CTLA-4 inhibitors in metastatic malignant melanoma. It will also observe whether specific biomarkers (host immune cells population, PD-L1 and IFNγ expression) correlate with the predominant composition of the gut microbiome and the response to treatment with immunotherapy.

Patients with metastatic malignant melanoma who will be treated with immunotherapy in the first line in the three-year period from October 2022 to October 2025 will be included in the research. One-hundred-and-fifty patients will be included. Consenting patients will be asked to provide clinical data and donate biological samples before, during and after completing their treatment. Patient data will be anonymized—date of birth, gender, date of diagnosis, performance status at initiation of treatment, liver enzymes, tumor markers—LDH, S100, localization, BRAF status, treatment type, response to immunotherapy, treatment time, immune-related adverse events of treatment.

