### 2.2. Study Objectives

#### 2.2.1. Primary Objectives

To determine the relationship between the predominant composition of the human gastrointestinal microbiome and the objective response to treatment with ICIs in patients with metastatic malignant melanoma.To determine whether the dynamics of exosomal mRNA expression for PD-L1 and PD-L1 on the surface of immune cells is related to the response to immunotherapy treatment and has predictive value.To determine whether the exosomal mRNA expression for IFNγ is related to the response to immunotherapy treatment and has a predictive value.

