#### 2.2.3. Exploratory Objectives

To determine if there is a relationship between a certain composition of the microbiome and the cell population (CD3+, CD4+, CD8+, the ratio between CD4+ and CD8+, macrophages) in the peripheral blood.Whether patients who develop immune-related side effects when treated with immunotherapy have a better response to it and longer survival without disease progression compared to patients who do not develop immune-related side effects.

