#### 2.5.4. Statistical Methods

The gastrointestinal microbiome, PD-L1 and Interferon Gamma expression will be correlated with one year of PFS as the primary outcome of the study. An interim analysis will be made after the first 20 included patients.

We will analyze the 16S rRNA sequences with the appropriate software tools from the Mothur software package, and we will perform analysis of molecular variance (AMOVA) and principal coordinate analysis (PCoA). For the statistical analysis of the differences in the representation of the sequences of individual bacterial groups in the studied microbiomes, we will use the DeSeq 2 package from the R programming environment. The association between phylogenetic diversity, taxonomic units, immune cells and the objective response to treatment will be determined using the Wilcoxon test. To compare values at different time points, we will use the paired *t*-test or corresponding non-parametric alternative. When comparing several groups at the same time, we will use the Kruskal–Wallis test. All differences will be considered statistically significant when *p* < 0.05.

The Kaplan–Meier method will be used to calculate survival (PFS), and the survival comparison of multiple groups will be calculated using the log-rank test. The association between the change in PD-L1 or IFNγ expression and response to treatment will be assessed using a logistic regression model and a multivariate model in which different variables will be included. Pearson’s or Spearman’s correlation test will be used to correlate changes in PD-L1 or IFNγ expression levels in tumor and blood.

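### The irAE comparison of PFS favours the irAE group by construction, and on-treatment change in PD-L1 or IFNγ is set against a response measured at the same time

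*Protocol article*

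**What the plan says.** **irAE and outcome.** Section 2.2.3 of the protocol article, an exploratory objective, asks whether patients with irAEs "have a better response to it and longer survival without disease progression compared to patients who do not develop immune-related side effects". For PFS, Section 2.5.4 states: "The Kaplan–Meier method will be used to calculate survival (PFS), and the survival comparison of multiple groups will be calculated using the log-rank test". It names no other survival method. Section 2.3.6 ends participation at progression. Section 2.3.7 records when each irAE began.

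**Biomarker change and response.** A primary objective in Section 2.2.1 asks whether the dynamics of PD-L1 "is related to the response to immunotherapy treatment and has predictive value". Section 2.5.4 gives the method: "The association between the change in PD-L1 or IFNγ expression and response to treatment will be assessed using a logistic regression model". The IFNγ primary objective does not mention dynamics; change in IFNγ enters only through that sentence. Section 2.5.4 also says that the markers "will be correlated with one year of PFS as the primary outcome of the study".

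**The concern.** Both questions use an exposure that becomes known only after treatment starts, and for neither does the article say that exposure must precede outcome. The mechanisms differ.

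(a) To be counted in the irAE group, a patient must remain progression-free until the irAE. A patient who progresses first falls into the no-irAE group by default. Progression-free time before the irAE is thus credited to the irAE group. At stake is a false finding that irAEs mark benefit. It would be readily believed, because Section 1.1 of the Introduction already presents a favourable association as background.

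(b) If marker change and response are read at the same visit, a marker that merely follows tumour burden will be associated with response. Reporting that as predictive value would misstate what a primary objective has shown.

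**Working it through.** The article gives no power calculation, event count or PFS assumption, so there is no figure to reproduce.

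**Part (a): inputs from the article.** 150 patients (2.1), 12 months of follow-up (2.3.6), scans at weeks 12 and 28 and on suspicion of progression (2.5.3), significance at p < 0.05 (2.5.4; two-sided assumed).

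**Assumptions not in the article.** Exponential PFS with one-year PFS of 40–50%; half the patients susceptible to irAE; mean onset 6–12 weeks; further scans at weeks 40 and 52; and, in one setting, 30% of progressions found clinically between scans.

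**Method.** Let T be the PFS time and X the irAE time, generated independently, so that the true hazard ratio is 1. A patient is in the irAE group if X < min(T, 12 months). With g the group indicator and p the proportion of the risk set in the irAE group, U = Σ(g − p) over progressions and V = Σp(1 − p). The hazard ratio is estimated by exp(U/V), and the test rejects if |U/√V| > 1.96. With 600 simulated trials per setting, the simulation standard error is at most √(0.5 × 0.5/600) = 0.02.

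| How progression is detected | Hazard ratio | False rejection (nominal 5%) |
|---|---|---|
| Continuously | 0.63–0.78 | 16–59% |
| 30% clinically, the rest at scans | 0.69–0.88 | 9–34% |
| Only at scans | 0.77–0.93 | 5–21% |

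A repeat run gave 19–61% for continuous detection and 5–31% for scan-based or mixed detection. The bias is larger with later onset, because more progression-free time must pass before a patient can enter the irAE group.

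The share of susceptible patients also matters. A wider set of runs used continuous detection and median PFS of 9 or 12 months, which is one-year PFS of 0.5^(12/9) = 40% or 0.5^(12/12) = 50%. With median onset of 1.5 months (mean 1.5/ln 2 = 2.2 months), rejection was 41–48% with half susceptible and 71–80% with 70% susceptible.

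**Corrected analyses under the same null.** A landmark at week 14, the end of the week-12 window, rejected in 4–7% of trials. In the wider set, irAE as a time-dependent covariate gave hazard ratios of 0.99–1.01 and rejection of 4.1–6.3%.

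**Part (b): the schedules side by side.**
- Blood (2.4.1): weeks 12 ± 2 and 28 ± 2, suspected progression, irAE.
- Scans (2.5.3): weeks 12 ± 2 and 28 ± 2, suspected progression, irAE, deterioration.

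Within one window a sample can fall up to 14 − 10 = 4 weeks after the scan, or 4 weeks before it. Nothing fixes the order.

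Selection adds to this. With constant hazard and an assumed one-year PFS of 45%, 150 × (1 − 0.45^(12/52)) = 150 × 0.168 ≈ 25 patients progress before week 12, and 150 × (1 − 0.45^(28/52)) = 150 × 0.349 ≈ 52 before week 28. Those detected before a scheduled visit contribute only samples triggered by progression or an irAE. Those detected at the week-12 scan contribute a sample taken alongside the outcome.

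As illustration only: a marker that does nothing but track tumour change at an assumed correlation of 0.3, 0.5 or 0.7, with half the patients responding, gives an AUC of about 0.63, 0.73 or 0.83.

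**The case against.** **The text does not assign log-rank to the irAE groups or state a time origin.** True. That patients are grouped as if irAE status were known at treatment start is an inference from the objective and the only survival methods named. Log-rank is compatible with a landmark, and an analysis plan that is not shown may specify one. What stands is that the article asks an ever/never question, names methods that need groups fixed at the time origin, and ends observation at progression. Followed as written, that is biased.

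**A reader might infer that the irAE analysis will very likely confirm a benefit that does not exist.** The documents do not support this. With early onset and progression found mainly at scans, false rejection can be close to nominal. Rates near 90% or above require later onset or a larger susceptible share, with continuous detection, and the article fixes none of these. The objective is also only exploratory.

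**A reader might call part (b) immortal-time bias, or say that early progressors have no on-treatment sample.** Neither is right. Part (b) concerns reverse causation and sampling triggered by the outcome. Section 2.4.1 and Table 1 provide a blood sample at progression. Section 2.5.4 speaks of association and does not pair a given sample with a given scan; a week-12 change could precede much of one-year PFS. What stands is that the regression has response as its outcome, has no ordering rule, and serves an objective that claims predictive value.

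**Conclusion.** The point holds in two separate parts.

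(a) For the exploratory irAE objective, the named methods bias PFS in favour of the irAE group. Under the stated assumptions, with half the patients susceptible, false rejection is about 5–60% against a nominal 5%, and the spurious hazard ratio is about 0.6–0.93. The size depends on irAE onset, the susceptible share and how progression is detected; the direction was the same in every setting.

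(b) For the primary objective on PD-L1 dynamics, and for the IFNγ change analysis in Section 2.5.4, the planned regression can show concurrent association but cannot by itself support a claim of predictive value. The article gives no basis for sizing this, and the AUCs above rest on assumed correlations.

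Analyses of baseline microbiome and baseline expression are not affected.

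**What to change.** - **irAE and PFS:** analyse irAE as a time-dependent covariate in a Cox model, using the recorded onset time. Show Kaplan–Meier curves and the log-rank test from a prespecified landmark at the week-12 assessment (for example week 14, when its window closes), with groups fixed by irAE status at that time. Use the same landmark for irAE against later response.
- **PD-L1 and IFNγ change:** relate baseline-to-week-12 change only to PFS or response after the week-12 assessment, in patients progression-free at that point. Report samples triggered by progression or irAE descriptively. Base any statement of predictive value on baseline values or on these landmark analyses.

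**Cost.** This changes analysis wording only; irAE onset is already collected and no visit or sample is added. Patients who progress by the landmark leave the dynamics analysis but stay in the baseline analysis. In the wider simulation set, with median PFS of 9 or 12 months, about 121 to 128 of 150 were still at risk at week 12. The time-dependent analysis also needs progression to be recorded after an irAE; since Section 2.3.6 allows participation to end for severe irAEs, the plan should say how PFS is handled in those patients.

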### 2.3. Recruitment and Eligibility of Patients

#### 2.3.1. Study Population

The study will recruit patients with metastatic melanoma (TNM classification, stage M) receiving first-line therapy with immune checkpoint inhibitors (ICIs). They will be treated with PD-1 inhibitors (pembrolizumab, nivolumab) or with a combination of PD-1 and CTLA-4 inhibitors (dual immunotherapy ipilimumab/nivolumab).

According to the phase III clinical research protocols that monitored OS and PFS in the treatment of metastatic malignant melanoma with ICIs, we will continue the treatment even if there is radiologically proven progress and the absence of clinical and biochemical signs of disease progression with sufficient suspicion of pseudoprogression.

#### 2.3.2. Inclusion Criteria

Age over 18 years;Cytologically or histologically verified malignant melanoma;Stage IIID unresectable/IV according to AJCC classification (8th edition, 2018);Performance status according to WHO 0–2 (ECOG criteria);1st line of systemic treatment with immunotherapy (nivolumab, ipi/nivo, pembrolizumab);Triple CT (head, thorax, abdomen)/PET CT done within 4 weeks before the first application;Signed consent to participate in clinical research.

#### 2.3.3. Exclusion Criteria

Previously treated melanoma with systemic therapy;Capacity status according to WHO 3–4 (ECOG criteria);Contraindications for immunotherapy treatment (known deficiency of the immune system or active immunosuppressive treatment or active autoimmune disease requiring treatment);Other malignant diseases (except cured basal cell carcinoma and squamous cell carcinoma).

#### 2.3.4. Recruitment Process

Only eligible patients with a signed consent form will participate in the study.

#### 2.3.6. Assessments during the Study

Patients will be followed up at their routine visits at the clinic. The follow-up will be scheduled at 3- or 4-week intervals, depending on the ICIs treatment regimen, when routine examination and laboratory test will be taken. Study-specific data will be collected at three different time points: up to 4 weeks before the start of treatment, at the 12th (+/−2 weeks) and 28th week (+/−2 weeks). Study-specific data will be taken additionally, if suspected disease progression and the appearance of immune-related adverse events or if indicated by the oncologist (Table 1).

Patients will be followed up regularly for the time of the treatment for the first 12 months. The study will be prematurely terminated in an event occurrence defined as disease progression/hyperprogression; by the physician’s choice in severe immune-related adverse events; when high doses of systemic corticosteroid (dexamethasone 4 mg/day or equivalent or higher) or prolonged antibiotic treatment are present; or by the patient’s choice. Before each stool sample donation, the patient will fulfill a questionnaire regarding eating habits, alcohol and tobacco consumption and medications. In the case of antibiotic treatment, the stool sample will be donated after 3 weeks of the last antibiotic dose taken.

#### 2.3.7. Immune-Related Adverse Events (IrAEs) Data Collection and Evaluation

Immune-related adverse events (IrAEs) will be reported at each follow-up visit. IrAEs will be evaluated based on the established and standardized grading system Common Terminology Criteria for Adverse Events (CTCAE) developed by the National Cancer Institute. This system grades adverse events based on their severity, ranging from grade 1 (mild) to grade 5 (death). Comprehensive and standardized data on irAEs will be obtained from the patient on each clinical visit, including relevant patient characteristics, timing of irAE onset, clinical manifestations, laboratory findings, imaging results and interventions undertaken. The biological samples from the patients will be taken if a grade 2 event or higher is noted by a physician. The biological samples will be taken within 2 weeks of the IrAE first reported. Results will be given as a percentage of incidence and the severity of IrAEs based on grading will also be reported.

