#### 2.2.2. Secondary Objectives

To determine whether a specific composition of the microbiome is associated with the occurrence of immune-related side effects in treatment with ICIS.To determine the effects of ICI on the gut microbiota over different time points.

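### irAE observation stops at progression or end of treatment, but irAEs are summarised as a crude percentage and no allowance for unequal time at risk is stated for the microbiome–irAE objective

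*Protocol article*

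**What the plan says.** **Objective.** Section 2.2.2 sets as a secondary aim: "To determine whether a specific composition of the microbiome is associated with the occurrence of immune-related side effects in treatment with ICIS".

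**Ascertainment.** Section 2.3.7 states: "Immune-related adverse events (IrAEs) will be reported at each follow-up visit". The items recorded include "timing of irAE onset, clinical manifestations, laboratory findings, imaging results and interventions undertaken".

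**Summary measure.** The same section ends: "Results will be given as a percentage of incidence and the severity of IrAEs based on grading will also be reported".

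**Length of observation.** Section 2.3.6 states: "Patients will be followed up regularly for the time of the treatment for the first 12 months". It then gives reasons for an earlier end, the first being progression: "The study will be prematurely terminated in an event occurrence defined as disease progression/hyperprogression". The others are a severe irAE (by physician's choice), high-dose corticosteroid, prolonged antibiotics and the patient's own choice.

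**Methods.** The only time-to-event method named in section 2.5.4 is for PFS: "The Kaplan–Meier method will be used to calculate survival (PFS), and the survival comparison of multiple groups will be calculated using the log-rank test". The remaining tests there (Wilcoxon, Kruskal–Wallis, paired t-test, logistic regression, correlation) take no account of how long a patient was observed. None is tied to the microbiome–irAE objective.

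**Exception.** Section 2.3.1 keeps some patients with radiological progression on treatment when pseudoprogression is suspected.

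**The concern.** Time at risk for an irAE is cut off by progression, which defines the study's primary outcome (one-year PFS, section 2.5.4). A patient who progresses at week 6 has been watched for 6 weeks; one who stays progression-free on treatment is watched for 12 months. If both are classed simply as with or without an irAE, the first is more likely to be classed as without, whatever the underlying irAE rate.

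The study's hypothesis is that the microbiome predicts response. If so, carriers of the favourable feature stay under observation longer and accumulate more recorded irAEs, even when the microbiome has no effect on irAE risk. The secondary objective could then report a toxicity-related microbiome that is only the responders' microbiome. The Discussion hopes to identify patients at higher risk of side effects before treatment starts, so such a result would be put to use.

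This differs from the exploratory comparison of response and PFS by irAE status (section 2.2.3). Here the irAE is the outcome.

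**Working it through.** The article gives no irAE effect size or power figure, so there is none to reproduce. The check asks how far a yes/no comparison goes wrong when the microbiome has no effect on irAEs.

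**Inputs from the article**
- 150 patients (section 2.1).
- Significance at p < 0.05 (section 2.5.4), taken as two-sided.
- Observation up to 12 months, ending at progression (section 2.3.6).
- irAEs in more than a third of patients (section 1.1), used as 35%, with 50% as an upper variant.

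**Assumptions not in the article**
- A binary microbiome feature splitting patients 75/75.
- One-year PFS by group.
- Constant hazards.
- Within each group, irAE and progression times are independent.
- A window *w* (3, 6 or 12 months) in which first irAEs can arise.

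**Formula.** With irAE hazard *l* (equal in both groups) and progression hazard *m* = −ln(one-year PFS)/12 per month:

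crude irAE proportion = *l*/(*l*+*m*) × [1 − exp(−(*l*+*m*)·*w*)]

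**Worked case.** PFS 60% vs 40%, *w* = 12, *l* set so that the average crude proportion is 35%.
- *m* = 0.0426 (favourable) and 0.0764 (unfavourable); *l* = 0.0529.
- Favourable: 0.0529/0.0954 × (1 − e^−1.145) = 0.554 × 0.682 = 37.8%.
- Unfavourable: 0.0529/0.1292 × (1 − e^−1.551) = 0.409 × 0.788 = 32.2%.
- Odds ratio = (0.378/0.622)/(0.322/0.678) = 1.28, although the true irAE hazards are equal.

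**Other cases at 35% crude incidence** (spurious odds ratio; false-positive rate of a two-proportion test, 3,000 simulated trials each):

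| One-year PFS | irAEs in first 3 months | first 6 months | whole 12 months |
|---|---|---|---|
| 50% vs 50% | 1.00; 4.7% | 1.00; 5.2% | 1.00; 5.1% |
| 60% vs 40% | 1.07; 5.1% | 1.14; 6.0% | 1.28; 10.8% |
| 70% vs 30% | 1.16; 7.8% | 1.32; 13.5% | 1.65; 30.8% |
| 80% vs 20% | 1.26; 11.0% | 1.56; 25.3% | 2.21; 63.6% |

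At 50% incidence the 12-month column becomes 15.0%, 46.2% and 82.9% false positives for the last three rows.

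**By progression hazard ratio.** Same formula with *w* = 12, overall one-year PFS 35–55%, and a 12-month irAE risk of 35–60% if nobody left early:
- Hazard ratio 0.5: odds ratio 1.26–1.52, false positives 10–24%.
- Hazard ratio 0.7: odds ratio 1.13–1.24, false positives 6–10%.

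**After the change.** A log-rank test on time to first irAE, censored at progression or 12 months, rejected in 4.4–5.9% of the simulated trials across all scenarios, against a nominal 5%.

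**Does cumulative incidence alone help?** If every patient is followed to an irAE, progression or month 12, cumulative incidence with progression as a competing event equals the crude proportion. A check at hazard ratio 0.5 gave identical values by both routes (22.8%, 27.6%, 38.9% and 48.7% in four settings), and the gap between groups remained (for example 26.7% vs 18.8%).

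**The case against.** **No test is tied to this objective.** A reader might infer that the plan will test the microbiome against irAEs with the crude percentage or a Wilcoxon test. The document does not say so. The sentence in section 2.3.7 concerns reporting, section 2.5.4 links the Wilcoxon test to objective response, and an analysis plan not shown may hold the detail. This stands. What remains is that the article fixes a summary measure and a follow-up rule that fit badly together, and that every non-PFS method it names ignores time at risk.

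**Not every response-related feature would look irAE-related.** That stronger reading is also tempting, and the figures contradict it. At 60% vs 40% PFS with early irAEs the false-positive rate is about 5%. At a hazard ratio of 0.7 it is 6–10% even with irAEs spread over the year. The size depends heavily on irAE timing, which the article does not give.

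**Observation may outlast radiological progression.** Section 2.3.1 keeps patients with suspected pseudoprogression on treatment, Table 1 lists irAE assessment at progression, and section 2.5.2 mentions OS. So it cannot be said that observation always ends at the first radiological progression. This softens the effect. It does not remove it, because no irAE visits after study exit are described.

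**The crude percentage is ordinary description.** This is accepted. It could be said to understate the one-year irAE risk, but only against a hypothetical risk with nobody progressing, which the article never claims to estimate.

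**Conclusion.** The concern holds in a limited form. As written, observed irAE occurrence depends on how long a patient stays progression-free and on treatment, and no stated method allows for this. A yes/no analysis of the secondary objective would be biased towards associating response-favourable microbiome features with more irAEs.

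The bias is negligible when irAEs arise early and the PFS link is no more than moderate, and small when the link is weak. It is material when the link is strong and irAEs are spread over the year. These sizes rest on assumed PFS and irAE rates, constant hazards, an even split of a binary feature, and independence of irAE and progression times within groups. The direction follows from the follow-up rule whenever the feature is linked to PFS.

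This affects a secondary objective and can be put right before analysis.

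**What to change.** 1. In section 2.5.4, state that baseline microbiome versus irAE is analysed as time to first irAE (grade 2 or higher, and any grade) with a cause-specific Cox model. Censor at the end of irAE observation: progression, end of ICI, study exit or 12 months. Adjust for or stratify by regimen (PD-1 inhibitor alone, or ipilimumab/nivolumab).
2. In section 2.3.7, keep the crude percentage by grade as description only, labelled as on-treatment incidence. Cumulative incidence may be added to handle patients censored for other reasons, but it does not by itself remove the bias.
3. Reconcile sections 2.3.1 and 2.3.6 on when irAE observation ends for patients treated past radiological progression, so that the censoring date is defined.

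**Cost.** Wording only: onset timing (section 2.3.7) and treatment time (section 2.1) are already collected. There is one more model to describe, and its hazard ratio must be read as the relative irAE rate while patients are still under observation, not as a ratio of overall one-year risks.
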